## Methods/design

### Study design

The present study design was a quasi-experimental design. Out of 147 National Primary Schools in Batu Pahat district, a total of 143 National Schools met the inclusion criteria of being co-educational, non-religious, non-special educational, multi-ethnic and government funded schools. Then, these 143 schools were stratified based on the three main school types, namely i) National Primary School (SK), ii) National Chinese Primary School (SJKC) and iii) National Tamil Primary School (SJKT). Two schools from each stratified group were selected. One school was selected as Intervention Group (IG) and one as Comparison Group (CG) from each school type. All children from these selected schools were invited to participate in the study.

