#### Socio-demographic background

In the present study, socio-demographic background of children in both intervention and comparison groups were determined. Children answered the items regarding their socio-demographic background, such as sex, ethnicity, age and date of birth, while parents answered questionnaires regarding parental education level and monthly household income.

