### Data analysis

The evaluation of the study was based on the modified intention-to-treat analysis to retain children in the study [44]. Children who fulfilled the following criteria would be included in the data analysis process:
i.Children of the intervention group who have attended at least two camps in the School Nutrition Programmeii.Children from both the intervention and comparison groups who had completed Pre-Intervention, Post-Intervention I and Post-Intervention II.

All statistical analysis will be conducted using IBM SPSS statistics 24.0. Descriptive analysis such as frequency and percentages, will be reported for categorical variables, while means and 95% confident interval will be reported for continuous variables. Skewness test of normality will be used to assess the normality of continuous variables. A value of skewness within the range of ±2.0 will be considered as normally distributed [45]. The Chi-square Test or Fisher’s Exact Test will be used to determine the association between two or more groups of categorical variables. The Independent sample t-test will be used to compare the mean values of the continuous variables between intervention and comparison groups and Paired sample t-test will be used to compare the mean values at pre-intervention and post-intervention within the intervention and comparison groups.

Simple linear mixed model will be conducted to determine the association of each covariate (such as time, group, child’s age, parental education level and school type) with all the dependent variables (namely knowledge, attitude and practice on nutrition, eating behaviour, physical activity, anthropometric measurement, psychological distress, cognitive performance and health-related quality of life). Multiple linear mixed model will be conducted to investigate the dependent variables between groups (intervention and comparison) over time, adjusted for covariates. Interaction term of time and group will be included in the model. The differences in all continuous variables between intervention and comparison groups will be determined at three time points (Pre-Intervention, Post-Intervention I and Post-Intervention II). The statistical significance will be set at *p* < 0.05. The data will be stored for future use after the completion of the study.

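### With complete three-visit data, covariates entered as main effects cannot adjust the group-by-time effect; the model needs covariate-by-time terms

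*Protocol article*

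**What the plan says.** The Study design section states "The present study design was a quasi-experimental design". On allocation it says "One school was selected as Intervention Group (IG) and one as Comparison Group (CG) from each school type", which makes six schools, three per arm. No randomisation is described.

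Under Socio-demographic background, the information collected covers "sex, ethnicity, age and date of birth, while parents answered questionnaires regarding parental education level and monthly household income".

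The Data analysis section describes two kinds of mixed model. The simple models relate one covariate at a time to each outcome, and the examples given are "such as time, group, child’s age, parental education level and school type". The effect model comes next: "Multiple linear mixed model will be conducted to investigate the dependent variables between groups (intervention and comparison) over time, adjusted for covariates". It is followed by "Interaction term of time and group will be included in the model". No other interaction is mentioned. The same section limits the analysis to children who completed all three assessments (intervention children must also have attended two or more camps). It also plans to compare the groups at each of the three time points.

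**The concern.** Nothing in the design balances child and family characteristics between the three intervention and three comparison schools, beyond pairing by school type. Covariate adjustment is therefore the main protection the article describes against confounding.

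The effect of interest is the time-by-group interaction, that is, whether the arms change differently. It is confounded by characteristics that affect the trend, for example if waist circumference or eating habits develop differently in boys and girls or in richer and poorer families. A main effect describes only a constant shift in level. If the covariates enter in that way, a table headed as adjusted would show group-by-time effects that are numerically unadjusted, and readers would credit them with protection they do not have.

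**Working it through.** **Inputs.** Non-randomised design with three schools per arm (Study design). Three assessments, all required for inclusion; covariate adjustment; one stated interaction (Data analysis). Planning figures from Sample size calculation: 195 per group, 80% response, mean waist changes of 0.1 and 2.2 cm.

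**The plan's own figures.** 195 / 0.80 = 243.75, rounded up to 244 per group; 2 × 244 = 488. These reproduce and are not in dispute. The planning difference is 2.2 - 0.1 = 2.1 cm.

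**Algebra.** For child *i* at visit *t*, let *G* be group, *z* a baseline covariate and *u* the child effect:

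Y_it = α_t + βG_i + δ_t G_i + γz_i + u_i + e_it, with δ_1 = 0.

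The change from the first visit is

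Y_it - Y_i1 = (α_t - α_1) + δ_t G_i + (e_it - e_i1).

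The term γz_i has cancelled. With every child seen at every visit, the estimate of δ_t is the difference between arms in mean change, whether or not *z* is in the model.

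Now suppose *z* also affects the trend, adding θ_t z_i with θ_1 = 0. The same estimate then targets

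δ_t + θ_t × (mean *z* in intervention - mean *z* in comparison).

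The second part is the confounding. Including γz_i does not touch it; including *z* by time does.

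**Numerical check.** One simulated data set per scenario, with all inputs assumed: 390 children (2 × 195), three visits, random child intercept and no true intervention effect. Sex and ethnicity shares are 60% against 40%, and mean income differs by 0.5 SD between arms. The base model has time, group, their interaction and age.

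| Scenario | Model | Group difference at baseline | Time × group, visit 2 | Time × group, visit 3 |
|---|---|---|---|---|
| Complete data, constant covariate effects | Base | 1.315 | -0.0562 | -0.3467 |
| | + sex, income, ethnicity as main effects | -0.1244 | -0.0562 | -0.3467 |
| | + the same, crossed with time | -0.103 | -0.0765 | -0.3907 |
| 20% of later visits missing | Base | 1.8896 | 0.5672 | 0.6118 |
| | + main effects | 0.1367 | 0.5703 | 0.6141 |
| | + crossed with time | 0.2399 | 0.3885 | 0.4583 |
| Complete data, income changes slope by 0.5 per visit | Base | 2.2798 | 0.0112 | 0.7579 |
| | + main effects | 0.3477 | 0.0112 | 0.7579 |
| | + crossed with time | 0.5653 | -0.1975 | 0.3140 |

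With complete data, main effects move only the baseline group difference. In the third scenario the built-in confounding is 0.5 × 0.5 = 0.25 at visit 2 and twice that, 0.50, at visit 3. The covariate-by-time terms shift the estimates by 0.0112 + 0.1975 = 0.2087 and 0.7579 - 0.3140 = 0.4439, close to those amounts. The remaining distance from zero is sampling noise in a single data set.

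**Size, as illustration only.** Bias = imbalance × difference in change. If low-income children gained 1 cm more waist and their share differed by 10 to 30 points, the bias would be 0.10 × 1 = 0.1 cm to 0.30 × 1 = 0.3 cm. That is 0.1 / 2.1 = 5% to 0.3 / 2.1 = 14% of the planning difference. Neither the 1 cm nor the imbalance comes from the documents, and the bias scales in proportion to each.

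**The case against.** A reader might infer that sex, ethnicity and household income are left out of the model, because they are collected but not among the named covariates. The text does not support that. The list is given as examples, it belongs to the sentence on the simple models, and the multiple model has no closed list. A condensed article may leave the exact set to a fuller document. That part of the objection stands, and the missing names are not the defect.

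It can also be said that a fuller document may specify covariate-by-time terms. It may. But the article is not silent on interactions: it names one, and a reader following it would fit only that one.

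Main effects are not useless either. They do adjust the planned comparisons of level at each time point, as the baseline column of the table shows. What they do not adjust is the difference in change.

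Finally, the design limits some imbalance. Schools are co-educational and paired by type, and parental education overlaps with income. This makes a large bias less likely without excluding one. Equally, nothing in the documents supports calling the schools hand-picked: they are said only to have been selected.

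**Conclusion.** The point holds as one about model form. In a non-randomised study analysed on children with all three visits, main-effect adjustment with time by group as the only interaction gives the group-by-time estimate no protection against covariate-related trends. This applies equally to the covariates already named.

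The exact equality assumes covariates fixed at baseline, the same children in both fits, and a covariance structure common to all children. It does not depend on the simulation's numbers. If children with missing income dropped out of the adjusted model the estimate would move, but through selection rather than adjustment. With some visits missing, the check showed practically no change from main effects.

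The size of any actual bias is unknown, and the 0.1 to 0.3 cm above should not be read as an estimate.

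**What to change.** In the Data analysis section, state that the multiple model for every outcome contains time (three levels), group and their interaction, plus one pre-specified set of baseline covariates, each with its interaction with time. The set would be age, parental education and school type, as already named, plus sex and household income. Add ethnicity only where it varies within school type. Say that the set does not depend on the results of the simple models. If a fuller document already fixes this, cite it.

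The data are already being collected, so the change is one of wording and model code. Each single-parameter covariate adds 3 - 1 = 2 interaction terms, and school type adds (3 - 1) × (3 - 1) = 4. A rule for missing parental income is needed, such as a missing category or imputation. The report should also say that child-level terms cannot remove differences in trend between schools, which three schools per arm leave unresolved.

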### Ethical approval

Ethical approval for this study was obtained from the National Medical Research Registry (NMRR) and Medical Research Ethics Committee (MREC) of Ministry of Health (MOH), Malaysia (NMRR-17-1273-36,187 IIR). Permissions for field data collection in primary schools were obtained from MOE Malaysia, State Department of Education of Johor, District Education Centre of Batu Pahat and selected schools before conducting the study. The researchers explained the study protocol to the children and their parents by using the information sheet. Prior to data collection, written consents were obtained from children, their parents/guardians, school authorities (principal and teachers), and canteen food handlers, respectively.

## Discussion

The present study will evaluate the effectiveness of a school-based intervention to prevent malnutrition among Malaysian primary school children. The three-month SNP that integrated nutrition education and healthy school food environment aimed to improve knowledge, attitude and practice on nutrition, eating behaviours, physical activity, cognitive performance and health-related quality of life; and to reduce BMI-for-age among primary school children. In order to achieve the primary outcomes of the present study, Koo and colleagues (2018) showed that a 12-week nutrition education intervention was enough to significantly increase practice of wholegrain foods consumption on a daily basis, lower body mass index-for-age z-score, body fat percentage and waist circumference among the intervention group, which was in line with previous study [46].

In Malaysia, several nutrition intervention programmes have been carried out among children aged 8 years [47, 48], adolescents [49] and children with overweight and obesity problem [50], which reported effectiveness of nutrition education intervention programmes in improving knowledge, attitude and practices on nutrition. The efforts were mainly for nutrition education promotion on healthy eating and physical activity. For instance, a 3-week Nutrition Education Programme among 8-year-old children in Malaysia aimed to improve nutrition knowledge, attitude, and practice found that knowledge and attitude had improved at post-intervention and 6-months follow-up, but practice score did not increase throughout the study in the intervention group over time [47]. Another Nutrition Education Programme by Zalilah et al. [28] focused among 8-year-old children showed that there were positive impacts on nutrition knowledge, attitude and practice after the intervention, but no follow-up result was reported after the programme. Zalilah et al. suggested that healthy family environment, healthy food availability and accessibility in schools should be included in nutrition intervention in order to sustain nutrition practices [48]. Tee et al. [31] also recommended that a successful nutrition intervention should include content and teaching strategies that are developmentally appropriate for the children and address changes in the environment. To date, there is no published study that focuses on promoting healthy school food environment in Malaysia. Therefore, it is important to develop an intervention that integrates nutrition education and school food environment, especially the school canteen that can exert a strong influence on children’s food decisions.

In Malaysia, primary school children consume their morning tea break during recess at school canteens, some children would take their lunch at school when they have tutorial classes or co-curricular activities. The Healthy School Canteen Guideline was developed and implemented by MOE Malaysia since year 2011. These guidelines aimed to improve the food service of school canteens and cultivate a balanced and healthy food intake in schools [32]. Based on the assessments of 113 primary school canteens in Batu Pahat district conducted in the year 2015, about one-third (33.6%) of the canteens were under the “Dissatisfactory” category, indicating non-compliance to the guidelines [51]. Most of the canteen caterers sold cordial drinks, carbonated drinks and fried foods especially processed foods like nugget, burger and hotdog; while insufficient green vegetables and fruits were prepared for the students [51]. Frederike et al. reported that the nutritional intake among United States school children was significantly affected by the school food environment because children spend many hours at school each day [52, 53]. A systematic review and meta-analysis stated the effectiveness of healthy school food environment in increasing the consumption of fruits and vegetables, while reducing total fat intake, saturated fat intake and sodium intake [54]. In order to increase healthy food availability in primary school canteens, it is important to address the concerns and knowledge of canteen food handlers [55]. However, Lessa et al. found that food handlers had a significantly lower food nutrition knowledge score than the general public [56]. Therefore, an integrate intervention, which includes collaboration between canteen food handlers and nutritionist is needed to ensure that appealing, healthy menu is prepared for the primary school children.

In Japan, besides serving nutritious food, the school lunch programme namely *Shokuiku* also serves as an important nutrition educational approach for school children to acquire proper nutrition knowledge, and to impart a sense of gratitude in children [57]. To the best of our knowledge, the present study is the first school-based nutrition intervention that integrates nutrition education and healthy school food environment among primary school children in Malaysia. This School Nutrition Programme is hypothesised to improve knowledge, attitude and practices on nutrition, eating behaviours, physical activity, anthropometric assessments, psychological distress, cognitive performance and health-related quality of life among Malaysia primary school children. Therefore, the examination on the effectiveness of a successful school nutrition approach within school setting is of great importance.

The sustainability of the intervention beyond the study duration will be considered through training of school teachers on the nutrition education curriculum and the transformation of school canteens by preparing a variety of nutritious menu for children during school recess. The World Health Organization reported that implementation of a comprehensive programme that promotes healthy school food environment, health and nutrition education and physical activity among school-age children and adolescents can end childhood malnutrition issues [1, 28]. Establishment of standards for meals provided in schools by increasing the availability of whole grains foods sold in schools that meet healthy nutrition guidelines and eliminate the provision or sales of unhealthy foods, such as sugar sweetened beverages and energy-dense, nutrient-poor foods, in the school environment are important. Previous local studies suggested that modifiable dietary habit strategies such as increasing fruits and vegetables intake, increasing whole grains intake, limiting consumption of sweetened drinks and controlling portion sizes were needed to combat childhood obesity [58, 59]. Importance of proper diets has been recognised not only for the control of lifestyle-related diseases, but more so in various physical aspects to improve the quality of life, including good growth of children [60].

Findings of the current study can be used by future researchers, health professionals, policy makers and school authorities to plan and implement the intervention in preventing malnutrition among primary school children in Malaysia. Furthermore, policy makers (including Parent Teacher Association), health agencies, programme planners and community leaders can use the data obtained from this study for planning and implementing effective policies as well as other intervention programmes that consist of nutrition education and healthy school food environment for Malaysian children to promote healthy lifestyle. The current study is important as it may raise awareness of the public, especially school teachers and canteen food handlers to give more attention towards the importance of nutrition education and healthy menu in canteens to Malaysian primary school children. This intervention study is in line with the National Plan of Action for Nutrition of Malaysia [NPANM] III (2016–2025), where nutrition education promotion is needed in schools and School Meal Programme has to be implemented to at least three schools by the year 2020 and at least six schools by the year 2025 in every state in Malaysia [61].

## Data Availability

Data sharing is not applicable to this article as no datasets were generated or analysed during the current study.

## Abbreviations

BMI: Body Mass Index
ISAK: International Society for the Advancement of Kinanthropometry
MOE: Ministry of Education
MOH: Ministry of Health
NHMS: National Health and Morbidity Survey
PTA: Parent Teacher Association
SNP: School Nutrition Programme
WHO: World Health Organization
